### Study activities and content

2.4.

To measure the stress, anxiety, and depression levels, baseline data collection was performed with the DASS21 questionnaire, which was developed by Lovibond and Lovibond (1995) [27]. The DASS21 questionnaire is a measurement scale for depression, anxiety, and stress, and is comprised of 21 questions. Studies tested DASS21 for reliability and validity with Cronbach's alpha reliability test for both clinical and non-clinical samples. The original version consisted of 42 items (DASS) and the short version consists of 21 items (DASS-21). The Bangla version of DASS21 was validated after using the translated questionnaire among medical students of Bangladesh [28]. DASS21 uses a self-reported scale of three sets of 7 items each, and is designed to measure the depression anxiety and stress. The depression scale evaluates dysphoria, hopelessness, devaluation of life, self-deprecation, lack of interest, anhedonia, and inertia. The anxiety scale measures autonomic arousal, muscle effects, situational anxiety, and anxious affect. The stress scale gauges chronic nonspecific arousal, difficulty relaxing, nervous arousal, and tendencies to be easily upset, agitated, irritable, over-reactive, and impatient [29],[30].

The patient's cortisol level, testosterone hormone level, and BMI were checked at baseline and at endline. The knowledge level of PCOS was evaluated in baseline and at the endline follow up using a validated knowledge questionnaire used in previous studies [20]. The endline data was collected after six months following the intervention.

The questionnaire was translated into Bangla and back-translated to English by the researcher. Then, the developed questionnaire was pretested among diagnosed PCOS participants selected from the gynecology department to check the feasibility, reliability, and validity of the questionnaire as a pilot. This was performed by the researcher and two research assistants. After resolving all issues, the finalized questionnaire was used to collect the data of the randomly recruited participants.

Testosterone (TT), Cortisol, BMI, and waist circumference were measured both in baseline and endline, which is 6 months after the baseline measurement.

The data is collected for both the intervention and control groups.

Two research assistants who were trained by the researcher, collected the data.

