### Sample size and power

2.9.

The sample size was calculated using G* power (version 3.1) for a repeated-measures analysis of variance (ANOVA) with a within-between interaction (F tests). The following parameters were used: two groups, two measurements, non-sphericity correction ε = 1.0, α = 0.05 (Type I error), and power = 0.80 (Type II error = 0.20).

The effect size f = 0.2319 was derived based on prior literature and our study design. Specifically, a previous study reported a Cohen's d of 0.44 [31] for similar outcomes. In our two-group repeated-measures design, the corresponding unadjusted effect size was calculated as follows:

f=d/2=0.44/2=0.22.

We planned to adjust for baseline covariates in the analysis. Assuming that covariates explain 10% of the variance in the outcome (ρ² = 0.10), the adjusted effect size is as follows:

$${\text{f}}_{\text{adj}}=0.22/\surd 1-0.10=0.2319.$$

Using these parameters in G*Power (F tests, repeated-measures ANOVA, within–between interaction), the calculated total sample size required to detect the prespecified effect size with 80% [32] power at α = 0.05 was 148 participants. To account for an expected 20% [33] attrition rate, the sample size was inflated as follows:

$${\text{N}}_{\text{adjusted}}=148/1-0.20=185.$$

Thus, the final recruitment target was 185 participants (93 in the intervention group and 92 in the control group) to ensure sufficient power for the primary analysis.

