All quantitative analyses will be conducted according to the intention-to-treat (ITT) principle, including all randomized participants in their originally assigned groups regardless of adherence to the intervention. The study adopts a two-arm parallel design (intervention and control) with a single primary outcome: participants demonstrating improvement from baseline to the endline score of DASS21. Continuous secondary outcomes, including testosterone and cortisol levels, knowledge scores, and BMI, will be analyzed using a two-way analysis of covariance (ANCOVA) with repeated measures, with the group (intervention and control) as a between-subject factor and time (pre- and post-intervention), and the group × time interaction testing whether the effect of time differs by the group. Potential confounding factors will be adjusted for, and a Bonferroni correction will be applied to account for multiple comparisons. Additionally, exploratory subgroup analyses will be conducted to assess the potential effect modification by age, baseline BMI, and baseline symptom severity. All statistical tests will be two-tailed, with the level of significance set at α = 0.05, unless otherwise specified.

This analytical strategy ensures methodological rigor by addressing statistical assumptions, minimizing false-positive findings, and providing a comprehensive assessment of the digital health education intervention's impact on the mental health and physiological outcomes of women with PCOS.

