## Missing data

8.

Efforts to minimize missing data will include thorough training of the study's personnel, regular data monitoring, and timely follow-ups with the participants to ensure complete and accurate data collection. Missing data for primary and secondary outcomes will be handled using multiple imputation methods, thereby incorporating baseline covariates (e.g., age, BMI, baseline DASS-21 scores, and group assignment) to generate plausible values under the assumption of missing at random (MAR). This approach minimizes bias and preserves statistical power compared with single imputation techniques such as last observation carried forward (LOCF). Sensitivity analyses will be conducted under alternative assumptions of MCAR and MAR to evaluate the robustness of the findings. The DASS-21 will be administered only at baseline and at the endline assessment, and no repeated measures will be collected during the intervention period.

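### With one pre and one post value, the group × time test for the continuous secondary outcomes is a change-score comparison: valid, but less efficient than adjusting the endline value for its own baseline

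*Protocol article*

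**What the plan says.** Section 4 (Quantitative analysis) states: "Continuous secondary outcomes, including testosterone and cortisol levels, knowledge scores, and BMI, will be analyzed using a two-way analysis of covariance (ANCOVA) with repeated measures". Group is the between-subject factor and time has two levels, pre and post. The treatment effect is read from the group × "time interaction testing whether the effect of time differs by the group". On covariates the section says only "Potential confounding factors will be adjusted for", without a list.

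There are two measurement occasions. Section 2.4: "Testosterone (TT), Cortisol, BMI, and waist circumference were measured both in baseline and endline, which is 6 months after the baseline measurement". The same section places the knowledge questionnaire at baseline and endline. Section 8 says of the primary instrument: "The DASS-21 will be administered only at baseline and at the endline assessment, and no repeated measures will be collected during the intervention period".

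Section 2.9 (Sample size and power) sizes the trial "for a repeated-measures analysis of variance (ANOVA) with a within-between interaction (F tests"), and describes the resulting target as serving the primary analysis. It also plans adjustment for baseline covariates, assumed to explain 10% of outcome variance. Section 4 names no model for the primary DASS-21 outcome.

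**The concern.** With one pre and one post value per participant, the interaction contrast is the difference between arms in mean change. The pre value sits in the model as a level of time, that is, as a response. Subtracting it in full fixes its regression slope at 1. ANCOVA on the endline value estimates that slope from the data. When r is below 1 and the variances are equal, the best slope is r, so full subtraction adds noise.

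At stake is precision. The intervals for cortisol, testosterone, knowledge and BMI may be wider than the collected data require, most of all where baseline and endline are weakly correlated. Section 2.9 extends the question to DASS-21, because it bases the sample size on an interaction test.

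**Working it through.** **Inputs from the protocol article.** d = 0.44, f = 0.22, 10% explained variance, N = 148, 20% attrition, inflated N = 185 (section 2.9); two-tailed α = 0.05 (section 4); 1:1 allocation (section 2.1); 212 enrolled (section 10). **Assumptions.** r is not given, so a range is used. Variances are equal at both times unless stated. d is in endline SD units. 212 × 0.80 = 169.6, taken as 169 evaluable.

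**1. The plan's own figure.** f = 0.22/√0.90 = 0.2319. With noncentrality λ = f²N on 1 and N−2 df, N = 148 gives λ = 0.05378 × 148 = 7.96 and power 0.800; 148/0.80 = 185. Both figures reproduce. That λ is the one for a plain two-group comparison. Putting f = 0.2319 into the interaction form 2f²N/(1−r) gives 76 at r = 0 and 40 at r = 0.5, so 148 did not come from that form.

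**2. Equivalence.** On one simulated data set (N = 148, r = 0.5), the interaction and the two-sample test on change scores both gave t = −3.631. ANCOVA on endline gave t = −4.254.

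**3. Variances.** Let the SDs be s0 at baseline and s1 at endline.
- Change: s0² + s1² − 2r·s0·s1, which is 2(1−r) in units of s² when s0 = s1.
- ANCOVA: s1²(1−r²), which is 1−r² in the same units.
- The difference between them is (s0 − r·s1)², which is never negative.
- With equal variances the ratio is (1−r²)/[2(1−r)] = (1+r)/2. The interval-width ratio is its square root.

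**4. Illustrative power, N = 169, d = 0.44, unadjusted α = 0.05.** N(d/2)² = 169 × 0.0484 = 8.18. λ = 8.18/[2(1−r)] for the interaction and 8.18/(1−r²) for ANCOVA.

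| r (assumed) | Variance ratio | Interval narrower by | λ interaction / ANCOVA | Power interaction / ANCOVA |
|---|---|---|---|---|
| 0.3 | 0.65 | 19% | 5.84 / 8.99 | 67% / 85% |
| 0.5 | 0.75 | 13% | 8.18 / 10.91 | 81% / 91% |
| 0.7 | 0.85 | 8% | 13.63 / 16.04 | 96% / 98% |
| 0.9 | 0.95 | 2.5% | 40.9 / 43.1 | both above 99% |

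**5. The 148 under each test.** If the 10% is explained by the outcome's own baseline, r = √0.10 = 0.316, and N(d/2)² = 148 × 0.0484 = 7.163.
- ANCOVA: λ = 7.163/0.90 = 7.96, power 80%. This is the same λ as in step 1.
- Interaction: λ = 7.163/(2 × 0.684) = 5.24, power about 62%. It would need N = 224 for 80%.

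Simulation at N = 148 (20,000 runs per case) agrees: 62.4% against 80.4% at r = 0.316, 76.4% against 86.9% at r = 0.5, and 92.7% against 95.9% at r = 0.7.

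**The case against.** The strongest reply is that the model is already called ANCOVA, that adjustment is promised, and that a condensed article may leave the covariate list to a fuller document. If the outcome's own baseline were a covariate with its own time interaction, the test would equal ANCOVA: change adjusted for baseline also gave t = −4.254. This makes the point conditional but does not remove it. The text makes the pre value a level of time and nowhere names the outcome's own baseline as a covariate for these tests.

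The power figures also have limits. d = 0.44 belongs to the sizing and is not given for any secondary outcome. Section 4 applies a Bonferroni correction, so α = 0.05 is not the level of those tests. Section 4 would also switch to rank tests if transformation failed, and then this model is not used. The figures are therefore illustrative; the variance ratio depends neither on d nor on α.

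A reader might infer three stronger things that the documents do not support:
- *The baseline is wasted, or the test is biased because randomization is simple and unstratified.* A change score does use the baseline, with slope 1. The test is unbiased over randomizations, and its error rate already allows for chance imbalance. The loss is of efficiency only.
- *Section 4 applies this test to DASS-21.* The sentence covers the continuous secondary outcomes. DASS-21 is reached only through section 2.9.
- *The trial has 62% power.* That holds for the interaction test at N = 148 and r = 0.316. Enrolment was 212, section 4 fixes no primary test, and section 2.9 does not say that the 10% comes from the outcome's own baseline.

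**Conclusion.** The point stands as an efficiency recommendation on a stated method for the continuous secondary outcomes. As written, the interaction test equals a change-score comparison. ANCOVA on endline has (1+r)/2 of its variance, given equal variances. The gain is material at low or moderate r and slight near 0.9, a value that is plausible for BMI but is an assumption. Apart from one degree of freedom, ANCOVA does not lose.

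For DASS-21 the conclusion is narrower. Section 2.9 names an interaction test, but its 148 is the number that a baseline-adjusted model needs for 80% power if baseline explains the assumed 10% of variance. On that reading, changing the named test leaves the number as it is.

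**What to change.** In section 4, replace the group × time test for each continuous secondary outcome with a linear model of the endline value on group plus the baseline value of that same outcome. Report the adjusted mean difference with a 95% CI. If the own-baseline covariate was always intended, say so and name it.

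State the model for DASS-21. If it is analysed as a continuous score, use the same baseline-adjusted model and name it in section 2.9 in place of the within-between interaction. State there that the 10% refers to the baseline score, if that is what is meant.

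The cost is wording only. The baseline values are collected, and section 10 reports that analysis has not begun, so the change can still be fixed in advance. No new data or participants are needed.

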## Qualitative analysis

5.

Qualitative data will be obtained through semi-structured in-depth interviews conducted post-intervention to explore the participants' experiences, perceptions, and behavioral changes in response to the digital health education platform. The purpose of this component is to gain deeper insight into how women with PCOS engaged with the intervention, perceived its usefulness, and navigated lifestyle and mental health behaviors during and after app usage.

All interviews will be audio-recorded (with participant consent) and transcribed verbatim. Field notes and observational memos will be maintained throughout data collection to capture contextual details. Transcripts will be anonymized by removing all personal identifiers to ensure confidentiality and ethical integrity.

The data will be organized and managed using NVivo or Atlas.ti software. A thematic analysis will be performed following the six-phase framework outlined by Braun and Clarke (2006), which includes familiarization with data, generation of initial codes, theme development, reviewing and refining themes, defining and naming themes, and producing the final report. Two independent researchers will separately code the data, and intercoder reliability will be assessed. Any discrepancies will be discussed until consensus is achieved, thus ensuring analytical reliability and validity.

The coding framework will be iteratively developed, thereby integrating both inductive (data-driven) and deductive (theory-driven) approaches to capture the breadth and depth of the participants' experiences. This process will allow for triangulation between quantitative outcomes and qualitative insights, thereby enhancing the overall interpretation and understanding of the intervention's effectiveness and acceptability.

## Attrition and post randomization bias

6.

Both groups continued to receive routine gynecological care from their attending physicians throughout the study period. The intervention group received additional support through the smartphone-based digital health education program and bi-monthly follow-up calls. The control group only received standard gynecological management but was counselled by research assistants to return for follow-up after 6 months. Although the frequency of physician follow-up in the control group varied, both groups maintained regular contact within the healthcare system to reduce differential attrition.

The frequency of gynecological follow-up in the control group was not standardized and may have varied among participants, which could influence the adherence or outcome assessments. However, efforts were made to reduce attrition bias by counselling all the control group participants to attend a 6-month follow-up and by maintaining an intention-to-treat analysis in data interpretation.

Although an intention-to-treat analysis and data imputation will be employed to minimize attrition-related bias, differences in dropout rates between the intervention and control groups may still introduce post-randomization bias. Future studies could reduce this risk by incorporating balanced engagement strategies for both groups.

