### Design

2.1.

This is a hospital-based intervention study that is prospective in nature and has two arms (1:1). This is a single blinded, single centered study where the participants were divided into either an intervention group or a control group. The participants were recruited from a rural private hospital of Bangladesh. The randomized controlled trial design strictly adheres to Consolidated Standards of Reporting Trial (CONSORT) [25] guidelines along with the Standard Protocol Items: Recommendations for Interventional Trial (SPIRIT) [26] guidelines. A schematic overview is shown in Figure 1.

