### Adherence to intervention

2.7.

The study maintained monthly follow-ups, during which the lead researcher contacted the participants in the intervention group. This regular engagement supported the participant's adherence to the intervention. Additionally, if a participant missed a scheduled reminder call from the researcher, the research assistants followed up with supplementary calls to ensure continued participation and compliance.

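### Active retention calls are described for the intervention arm only, the claimed balance of contact is not supported, and outcome-related dropout would go untested

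*Protocol article*

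**What the plan says.** Section 2.7 (Adherence to intervention) has the lead researcher telephoning intervention women throughout the six months. If a call was missed, "the research assistants followed up with supplementary calls to ensure continued participation and compliance". Section 2.8 (Control group) gives controls usual gynecological care and an endline visit, and Table 1 shows nothing for them between the baseline and final sessions. Section 6 (Attrition and post randomization bias) adds that the research assistants advised controls to come back at six months.

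Section 6 then offers a safeguard: "both groups maintained regular contact within the healthcare system to reduce differential attrition". Its next paragraph says: "The frequency of gynecological follow-up in the control group was not standardized and may have varied among participants". The same paragraph lists the ITT analysis among the efforts against attrition bias. The section closes by accepting that unequal dropout could still cause bias, and adds: "Future studies could reduce this risk by incorporating balanced engagement strategies for both groups".

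Sections 4 and 8 plan multiple imputation under MAR, using baseline covariates that include baseline DASS-21, together with group. Sensitivity analyses are named under MCAR and MAR. DASS-21 is taken at baseline and endline only. Section 10 says that endline collection began in November 2025 and that analysis had not started.

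**The concern.** The only active measure described for keeping women in the study operates in one arm. The routine care cited as a balancing factor went to both arms, so it cannot offset calls added to one of them. Its frequency among controls is also said to have been uncontrolled.

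A woman lost before endline has no post-baseline DASS-21 at all. ITT fixes the arm in which she is analysed but does not supply her score. Imputation supplies one only on the assumption that, given baseline covariates and arm, lost women resemble retained women. If they do not, and more controls than intervention women are lost, the between-arm difference is shifted. If lost women are the more distressed, the benefit is understated; if they are the less distressed, it is overstated. MCAR is a stronger assumption than MAR, so neither named sensitivity analysis moves towards this possibility.

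**Working it through.** **The plan's own figures.** Section 2.9 gives "α = 0.05 (Type I error), and power = 0.80 (Type II error = 0.20"). Section 4 says: "All statistical tests will be two-tailed". Section 2.9 also says: "The effect size f = 0.2319 was derived based on prior literature and our study design".

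- f = 0.44/2 = 0.22, and 0.22/√0.90 = 0.2319.
- A noncentral F with 1 and N − 2 degrees of freedom and λ = f²N first reaches 80% power at N = 148 (power 0.800).
- 148/(1 − 0.20) = 185. Both stated totals reproduce.
- Enrolment was 212 (106 + 106). The 20% attrition is an overall figure; no split by arm is given.

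**Does unequal loss cost power?** Hardly. The splits below are assumptions that average 20% of the 106 + 106 enrolled. Power is from the noncentral t at d = 0.44.

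| Loss, intervention / control | Completers | Power |
|---|---|---|
| 20% / 20% | 85 + 85 | 0.81 |
| 15% / 25% | 90 + 80 | 0.81 |
| 10% / 30% | 95 + 74 | 0.81 |
| 5% / 35% | 101 + 69 | 0.80 |

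**Does unequal loss alone cause bias?** Not under MAR. In 2,000 simulated trials of 212 women, the true effect was −0.44 SD, the baseline–endline correlation was 0.5, and dropout depended on arm and baseline only (about 11% and 30%). The baseline-adjusted estimate among completers averaged −0.438, against −0.381 for the unadjusted completer difference. Conditioning on arm and baseline, as the planned imputation does, removes this kind of bias.

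**When does bias arise?** Let p be the proportion lost in an arm. Let δ be the endline gap, lost minus retained, that baseline covariates and group do not explain. The full-arm mean is then the retained mean plus pδ, so a MAR analysis misses the arm mean by pδ. With the same δ in both arms:

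bias = (p_control − p_intervention) × δ

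The documents give neither the loss difference nor δ, so both are assumed:

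| Loss difference | δ = 0.25 SD | δ = 0.50 SD | δ = 0.75 SD |
|---|---|---|---|
| 5 points | 0.0125 | 0.025 | 0.0375 |
| 10 points | 0.025 | 0.05 | 0.075 |
| 20 points (10% vs 30%) | 0.05 | 0.10 | 0.15 |

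Against d = 0.44, the lowest cell is 0.0125/0.44 = 2.8%, the centre 0.05/0.44 = 11.4% and the highest 0.15/0.44 = 34.1%. If δ = 0, every cell is zero.

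If δ differs by arm, bias = p_control × δ_control − p_intervention × δ_intervention. Equal loss then does not guarantee zero: at 20% in each arm, δ_control = 0.5 and δ_intervention = 0 give 0.20 × 0.5 − 0.20 × 0 = 0.10 SD. A sensitivity analysis should therefore let the shift differ by arm.

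**The case against.** The strongest reply has five parts.

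- **Controls received some retention effort.** They were advised to attend at six months, and section 8 mentions prompt follow-up of participants without limiting it to an arm. This stands: the imbalance is in active calls, and a reader who inferred that controls had no retention effort would go too far. Section 8 nevertheless sets out no call or tracing step for controls.
- **The calls are part of the treatment.** The abstract, discussion and limitations present them so, and the back-up calls serve adherence as well as participation. This also stands. Unequal contact during the six months follows from comparing app plus calls with usual care, and need not be removed. It is no reason for tracing at endline to be unequal.
- **The safeguard sentence is concessive.** It admits varying frequency and refers to routine care. Variable contact is not absent contact, so reading the section as proof that the safeguard did not exist is too strong. What stands is that the text does not support regular contact as a balance against differential attrition.
- **The risk is disclosed, and ITT is at one point paired with imputation.** True, but disclosure does not correct the credit given to ITT on its own, and it does not test the risk.
- **Tracing detail may sit in the full protocol, and the endline window may largely have passed.** Both are possible. The article does, however, state its step for controls and defer balanced engagement to later research, and it reports endline collection as begun with analysis not started.

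**Conclusion.** The point holds in a limited form. Active retention contact is unequal by arm, the stated balance of contact is not supported by its own section, and ITT is credited with something that it cannot do. Differential, outcome-related loss is therefore possible, and the named sensitivity analyses would not show it.

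A reader might infer that dropout will differ by arm and will bias the DASS-21 comparison. The documents do not support that: they report no dropout by arm, section 6 speaks only of a possibility, and unequal loss by itself neither biases a MAR analysis nor costs appreciable power.

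The size of 0.01 to 0.15 SD rests wholly on the assumed loss differences and unexplained gaps, with the gap taken as equal in both arms. Its upper end needs both a 20-point difference and a 0.75 SD gap left after baseline adjustment. The point is worth correcting because the remedy is cheap; it does not invalidate the trial.

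**What to change.** 1. For the endline still being collected, use one tracing procedure in both arms: the same number and spacing of reminder and missed-visit calls, made by the research assistants from one script without intervention content. Apply it to every woman without an endline DASS-21, including those who stopped using the app.
2. Replace the regular-contact sentence in section 6 with a statement that contact during the six months differed between arms by design. Reconcile the call frequency, which is monthly in sections 2.7 and 12 but bi-monthly in the abstract and sections 2.10 and 6, so that the difference in contact can be described.
3. Stop listing ITT as a measure that reduces attrition bias. Say that it preserves the randomized groups and that missing endline scores are handled by imputation under MAR.
4. Report endline completion and reasons for loss by arm.
5. Add a delta-adjusted MNAR sensitivity analysis to the multiple imputation, with the shift allowed to differ by arm and its range fixed before analysis starts.

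The cost is a few short calls by existing staff, some rewording and one further analysis. The drawbacks are minor extra contact for controls near endline, and little effect on women whose endline window has already passed. For those women, items 4 and 5 carry the weight.
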